### Treatment procedure

For eligible participants, approximately 8 mL of bone marrow aspirate will be collected from the posterior iliac crest into a heparinised syringe under either local or general anaesthetic. A decision on which technique will be used will depend on discussions with the patient. MSC processing and manufacturing will be at the cell-processing centre at the Centre for Cell Gene and Tissue Therapeutics based at the Royal Free Hospital in London. The cells are cultured using a standardised protocol using fetal calf serum in the culture medium with robust validation systems to confirm quality and sterility of cells. Approximately 5 weeks after bone marrow harvest, participants will undergo implantation of the culture expanded MSCs under local anaesthetic in the outpatient setting following clinical assessment and tendon imaging using conventional ultrasound and UTC measurement.^27^

A single injection of between 4 and 20×10^6^ MSCs suspended in 1 mL of Dulbecco’s Modified Eagle Medium will be injected under ultrasound control by a delegated, experienced and trained radiologist along the length of the tendon at the area of greatest degeneration starting just distal to the degeneration and finishing just proximal to normal structure. Participants will be observed for a minimum of 2 hours after implantation for any immediate adverse effects.

All participants will be referred for a standard course of physiotherapy. The physiotherapist will issue a discharge summary following their treatment and a copy of this will be included in the participant record. This summary includes details on participant compliance.

### Subsequent assessments

Subsequent assessments following the MSC implantation include AE review, VAS (pain), MOXFQ, VISA-A Questionnaire, EQ-5D, SAS Questionnaire, ultrasound imaging (conventional ultrasound and UTC) and clinical assessment (table 1). These will occur at 6, 12 and 24 weeks post-MSC implantation. After 2 days, the trial coordinator will phone the patient to check they are well and record any AEs on the ASCAT case report form. The trial will end on the last visit of the last precipitant.

### Patient and public involvement

Patients and the public were not directly involved with the development of the current protocol. The primary research question is the safety of use of culture expanded MSCs. This will enable the development of a larger RCT that will involve oversight from the patient and public representatives. Patient recruitment is described above and the results will be disseminated to the participants via a news letter.

### Power and sample size

Sample size was determined to ensure a predetermined level of accuracy for the incidence of SAR using an exact binomial CI. With 10 participants, if no SAR is observed we can rule out a true SAR rate of 31% or greater with 95% confidence, or a true SAR rate of 21% or greater with 80% confidence, or a true SAR rate of 13% or greater with 50% confidence. With six participants for the interim analysis, if no SAR is observed we can rule out a true SAR rate of 46% or greater with 95% confidence, or a true SAR rate of 32% or greater with 80% confidence, or a true SAR rate of 21% or greater with 50% confidence. Since the study is a proof-of-concept pilot study, no formal power calculation was performed.

### Statistical analysis

The findings from this study will be published and the data will also be included in subsequent larger trials if appropriate. Baseline data collected and summarised will include: participant gender, age, height, weight, body mass index, duration of symptoms, sporting activity, smoking/non-smoking, medication, any other musculoskeletal problems, EQ-5D, MOXFQ, VAS (pain), SAS score, VISA-A score and ultrasound findings (conventional ultrasound and UTC findings).

Continuous baseline data will be presented as mean and SD for normally distributed variables, medians and IQRs for non-normally distributed variables and frequencies and percentages for categorical baseline variables. For the primary outcome, the proportion of participants experiencing a SAR at any time over the 24-week follow-up period will be calculated along with exact binomial CIs to express the uncertainty in the observed incidence rate of SAR.

Since the primary outcome is the incidence of SARs, missing outcomes are not anticipated. The primary analysis will be as per-protocol. All participants will receive the same treatment, which cannot be withdrawn once given and we will only analyse the data from the participants who actually receive autologous culture expanded MSCs. Cancellation of implantation will be a logistical rather than surgical decision and as such is not expected to introduce bias. The proportion of participants experiencing a success at 6 months will be calculated along with exact binomial CIs to express the uncertainty in the observed incidence of success at 6 months. Changes from baseline in EQ-5D, MOXFQ, VAS (pain), VISA-A and SAS scores will be summarised as mean and SD if normally distributed, or median and IQR if the data do not demonstrate normality.

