**Figure 1 F1:**
[figure not shown]
Trial flow diagram. AT, Achilles tendinopathy; EQ-5D-5L, EuroQol 5-dimension 5-level; GMP, good medical practice; MOXFQ, Manchester Oxford Foot and Ankle Questionnaire; NHS, National Health Service; SAS, Sporting Activity Score; UTC, ultrasound tissue characteristics; VAS, Visual Analogue Score; VISA-A, Victorian Institute of Sports Assessment Achilles Questionnaire.

The primary outcome will be safety as defined by the incidence rate of serious adverse reaction (SAR). The secondary outcomes will be efficacy as measured by patient-reported outcome measures. Ultrasound techniques will assess the radiological outcome of the procedure. Computerised ‘ultrasound tissue characterisation’ (UTC) is also carried out in order to add in a less subjective assessment. UTC involves a precision instrument that moves the ultrasound probe automatically across the long axis of the Achilles tendon collecting transverse images at even distances of 0.2 mm over a length of 12 cm and enable tomographic visualisation and tissue characterisation and quantification of architecture and integrity of the collagenous matrix.

Ultrasound examinations undertaken in this study will performed by a musculoskeletal radiologist with experience of undertaking such an examinations. The end of the Autologous Stem Cells in Achilles Tendinopathy (ASCAT) trial is the last visit of the last participant.

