### Baseline assessment

Baseline assessments to be carried out on day 0, immediately prior to harvest include:Clinical assessment;Baseline questionnaire on demographics and comorbidity/concomitant medication;Victorian Institute of Sports Assessment Achilles (VISA-A) Questionnaire;Visual Analogue Score (VAS);Manchester Oxford Foot and Ankle Questionnaire (MOXFQ);EuroQol 5-dimension 5-level (EQ-5D-5L) Questionnaire;Sporting Activity Score (SAS);Ultrasound imaging and UTC;Adverts events (AE) review.

Table 1 shows all the planned assessments and procedures that will be performed before MSC implantation.

**Table 1 T1:** Schedule for assessments

	Screening	Bone marrow harvest*	Baseline (immediately before implantation)	Implantation	Follow-up			
Visit number	1	2	3		4	5	6	7
Timing postimplantation		Approximate week: 5	Day 0		Day 2†	Week 6	Week 12	Week 24
Deviation window (days)	‡	±14	0		0 hours	±7	±7	±7
Eligibility review	X		X					
Medical history	X							
Informed consent	X							
Clinical assessment	X		X					
HBV, HCV, HIV-1 and HIV-2 and syphilis tests	X							
Pregnancy tests	X§	X	X¶					
Bone marrow harvest		X						
MSC implantation				X				
Routine course of physiotherapy						X**	X**	X**
Ultrasound imaging (conventional ultrasound and UTC)			X**			X††	X††	X††
VISA-A Questionnaire			X			X	X	X
VAS			X			X	X	X
MOXFQ			X			X	X	X
EQ-5D Questionnaire			X			X	X	X
SAS Questionnaire		X						X
Concomitant medication	X	X	X	X	X	X	X	X
AE review		X	X X		X	X	X	X

*Urine pregnancy test at bone marrow harvest.

†Day 2 follow-up assessments are done by telephone.

‡Screening procedures must take place at least 1 week before and within 30 days of the bone marrow procedure.

§Self-declaration from the patient.

¶Within 7 days of implantation.

**The number of visits are dependent on participant’s progress and are not obligatory at these time points. Standard NHS protocol for physiotherapy will start within 1–2 weeks after implantation. Dates of physiotherapy attendances will be recorded in the case report form.

††Two radiologists will independently scan the participant using ultrasound. UTC will also be measured twice on each occasion.

AE, adverse events; EQ-5D-5L, EuroQol 5-dimension 5-level; HBV, hepatitis B virus; HCV, hepatitis C virus; MOXFQ, Manchester Oxford Foot and Ankle Questionnaire; SAS, Sporting Activity Score; UTC, ultrasound tissue characteristics; VAS, Visual Analogue Score; VISA-A, Victorian Institute of Sports Assessment Achilles Questionnaire.

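### The only safety proportion described covers implanted participants, so serious harm from marrow harvest can go uncounted, and the visit schedule contradicts the reason given for the restriction

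*Protocol article*

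**What the plan says.** Under Statistical analysis, the primary result is "the proportion of participants experiencing a SAR at any time over the 24-week follow-up period", with an exact binomial confidence interval. The set is fixed in two statements: "The primary analysis will be as per-protocol" and "we will only analyse the data from the participants who actually receive autologous culture expanded MSCs". The reason given is: "Cancellation of implantation will be a logistical rather than surgical decision and as such is not expected to introduce bias".

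Under Treatment procedure, bone marrow is taken from the posterior iliac crest "into a heparinised syringe under either local or general anaesthetic". Implantation follows about 5 weeks later, after the cells have been cultured and checked for quality and sterility.

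Table 1 (Baseline assessment) marks an adverse event review at the harvest visit. At the visit just before implantation it repeats the eligibility review and clinical assessment, and it requires a pregnancy test, footnoted "Within 7 days of implantation". Box 1 makes pregnancy an exclusion, tested before both harvest and administration.

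On timing, Subsequent assessments says of the follow-up assessments: "These will occur at 6, 12 and 24 weeks post-MSC implantation".

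**The concern.** The treatment has two steps, and the first is an invasive procedure done only to make the product for the second. Study design says the trial's primary role is to demonstrate safety and that its results will inform a later phase III trial. A reader of the final report will want the risk of the whole course, from harvest onward.

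The stated rule gives no place to a participant who is harvested and not implanted. If a serious harvest complication is the reason for not implanting, that person leaves both numerator and denominator. The only defence offered is that cancellation is logistical. If that fails, the set is chosen partly on what happens after the first trial procedure. With 10 participants, one person changes the picture.

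**Working it through.** **1. The plan's own figures.** Power and sample size gives upper limits for zero SARs. The two-sided exact (Clopper-Pearson) upper limit with zero events is 1 − (α/2)^(1/n).

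| n | Confidence | Calculation | Result | Stated |
|---|---|---|---|---|
| 10 | 95% | 1 − 0.025^(1/10) | 30.85% | 31% |
| 10 | 80% | 1 − 0.10^(1/10) | 20.57% | 21% |
| 10 | 50% | 1 − 0.25^(1/10) | 12.94% | 13% |
| 6 | 95% | 1 − 0.025^(1/6) | 45.93% | 46% |
| 6 | 80% | 1 − 0.10^(1/6) | 31.87% | 32% |
| 6 | 50% | 1 − 0.25^(1/6) | 20.63% | 21% |

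All six are reproduced. The arithmetic is sound for 10 and 6 analysed participants.

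**2. Is cancellation only logistical?** The routes to non-implantation that the article itself sets up are:

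- Repeat eligibility review and clinical assessment before implantation (Table 1): a medical route.
- Pregnancy test before implantation (Table 1, Box 1): a medical route.
- Quality and sterility checks on the cells (Treatment procedure): a product route, which some would call logistical.

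At least the first two are not logistical, so the sentence is too absolute. A harvest complication could act through the first.

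**3. When does the 24-week window open?** Statistical analysis does not say. Table 1 times visits from implantation, and Subsequent assessments counts 6, 12 and 24 weeks from it. Harvest, about 5 weeks earlier, would then fall before the window. The text above Table 1 instead puts day 0 just before harvest, so the start is an inference. The consequences are:

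- Window from implantation: a serious harvest event is missed in implanted and non-implanted participants alike.
- Window from harvest: such an event could count in an implanted participant, if SAR covers harvest. In a non-implanted one it is still missed, because of the set.

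**4. Illustration.** The documents give neither a harvest event rate nor a number not implanted, so these are assumptions. Intervals are 95% two-sided exact.

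| Assumed course | Plan's proportion (no SAR after implantation) | Whole-treatment proportion |
|---|---|---|
| 10 harvested, 1 serious harvest event, that person not implanted | 0/9, upper limit 33.6% | 1/10, 0.3 to 44.5% |
| 10 harvested and implanted, 1 serious harvest event, window from implantation | 0/10, upper limit 30.8% | 1/10, 0.3 to 44.5% |
| 10 implanted plus 1 harvested only, who has the event | 0/10, upper limit 30.8% | 1/11 = 9.1%, 0.2 to 41.3% |
| 10 implanted plus 2 harvested only, one with the event | 0/10, upper limit 30.8% | 1/12 = 8.3%, 0.2 to 38.5% |

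**5. Precision if fewer than 10 are implanted, no events.** 9 implanted: 1 − 0.025^(1/9) = 33.6%. 8 implanted: 1 − 0.025^(1/8) = 36.9%.

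**The case against.** The strongest reply is that the plan answers the question it asks. Patient and public involvement puts the primary question as the safety of culture expanded MSCs, and the outcome is an adverse reaction, not any adverse event. Someone who never received cells cannot react to them, so leaving that person out does not bias a cell-specific rate. This stands. For that rate the implanted set is defensible and should be kept.

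A reader might go further and infer three things that the article does not support.

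- *That the SAR proportion is biased downward.* This would follow only if SAR includes reactions to harvest or anaesthesia. The article does not say what a SAR is a reaction to. If it means the cells alone, 0/9 and 1/10 are different endpoints, and the second is not a corrected version of the first.
- *That the stated precision is wrong or will not be delivered.* The figures are conditional on 10 or 6 participants and are correct on that condition. Whether a non-implanted participant is replaced is a detail that an article may leave to the full protocol.
- *That harvest adverse events are thrown away.* Table 1 schedules their review, and a condensed article need not describe every safety listing. What can be said is narrower: the analysis rule, as worded, has no place for people not implanted.

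It can also be said that failed cells are a production matter and that pregnancy has no evident link to a reaction to cells never given. Both are fair for the cell-specific rate. Neither rescues the general claim that cancellation is logistical, and neither deals with a harvest complication that stops implantation.

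**Conclusion.** The point holds as one about coverage and justification. The implanted-only SAR proportion is acceptable as the cell-specific rate. It cannot stand as the only safety result for a treatment that every participant enters through marrow harvest. The sentence defending the restriction conflicts with the pre-implantation checks in Table 1 and Box 1.

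The size is illustrative: one serious harvest event among 10 harvested is the difference between reporting no event (upper limit 33.6% with 9 implanted, 30.8% with 10) and a whole-treatment proportion of 10% (0.3 to 44.5%). This assumes that such an event occurs, which the documents neither predict nor exclude. The case in which the affected person is still implanted also assumes that the window opens at implantation, or that SAR excludes harvest. The case in which that person is not implanted needs neither assumption, because the population rule alone removes the event.

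**What to change.** Change the analysis wording; no trial procedure is affected.

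1. Keep the SAR proportion in implanted participants with its exact interval, label it the cell-specific rate, and state when its 24-week window opens and what a SAR is a reaction to.
2. Beside it, report a whole-treatment safety proportion with exact interval. The denominator is all participants in whom harvest was started. The numerator is those with a serious event related to harvest, anaesthesia or cells, from harvest to week 24 after implantation. For participants not implanted, state where their observation ends.
3. List every non-implantation with its reason, and remove the claim that cancellation is only logistical and not expected to introduce bias.
4. If fewer than 10 are implanted, quote the limit for the number analysed (33.6% for 9, 36.9% for 8, with no events).

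The cost is small: wording, one more proportion and a short listing. Adverse event review is already scheduled at harvest, though recording for participants who are not implanted should be confirmed. The downside is a possibly less favourable safety figure beside the cell-specific one.

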## Ethics and dissemination

The findings of this study will be disseminated through peer-reviewed publications and conference presentations.
